## Data Management And Analysis Plan

*All data management and statistical analyses will be performed at BIDMC under the direction of the senior biostatistician. Analyses will be performed primarily using SAS statistical software.*

To protect confidentiality, all data will be stored a locked file cabinet located in a secured office in the Division of General Medicine and Primary Care at BIDMC staffed by research personnel. All computers and data files will be password protected. All data processed will be in aggregate form and every study subject will be assigned a unique identification number. The Master List linking subject names to their ID numbers will be maintained in a locked cabinet in the Project Director’s office.

All data, such as eligibility criteria, questionnaires, laboratory values, and results of cardiac testing will be entered electronically and verified for accuracy by a second research assistant who is not blinded to study group. At regular intervals, collected data will be checked for completeness and appropriate ranges of numerical data. All primary data including data collected in paper form will be stored in locked file cabinets in an office staffed by research personnel from this study. Back-up files of all computerized databases will be maintained in the Division of General Medicine and Primary Care under the direction of the biostatistician. Data will be rigorously managed by the biostatistician and project manager to confirm data completeness and quality.

### Analysis Plan for Primary Specific Aims

To assess the adequacy of randomization, we will use Fisher’s Exact tests (categorical variables, e.g., sex, NYHA Class) and Wilcoxon rank-sum tests (continuous variables, e.g., age) to detect any differences in baseline characteristics between treatment groups.

Our three primary endpoints are change in exercise capacity and quality of life from baseline to 12 weeks using the six-minute walk, peak VO2 and MLHF score. Because we will recruit patients from 3 institutions, we will formally examine whether there is a site effect by performing Kruskall-Wallis tests to assess whether changes from baseline to 12 weeks differ by site for each outcome. In the event that we observe a site effect, we will proceed stratifying our analyses by site using van Elteren’s test. A priori, however, we do not expect to observe a site effect for a number of reasons, including the 3 institutions are academic tertiary care centers located in the same catchment area, they have similar patient profiles, and they apply the same standard of cardiac care by following ACC/AHA guideline. If no site effect is observed, we will proceed with our analyses by performing two-sample non-parametric Wilcoxon rank-sum tests to compare the distribution of change from baseline to 12 weeks between treatment and control groups for each outcome measure.

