## 2. STATISTICAL CONSIDERATIONS

### Sample Size Justification

We will enroll a total of 100 patients, with 50 patients in each group. We estimate that 75 of patients will be enrolled from BIDMC and 25 patients from other study sites (eg. BWH and MGH).

The sample size is based on power calculations using data from our pilot study. For these calculations, we assumed a 1) 10% loss of efficiency because we will use non-parametric tests and 2) 20% dropout rate. Although all patients enrolled in the pilot study completed that study, we did have a few missing data points. Therefore we felt it would be prudent to anticipate a larger dropout rate given prior experiences with HF patients.

Since there are three primary endpoints (change in six-minute walk, peak VO2, MLHF score), we will apply a Bonferroni adjustment to preserve the 5% level of significance. Based on pilot data, the standard deviation (SD) for change in walk test distance=317 feet; SD for change in peak VO2=2.1 ml/kg/min; and SD for change in MLHF score=17 points. Accounting for the above, the sample of 50 patients per group provides 80% power to detect a peak VO2 difference of 1.5 ml/kg/min between groups. We will have >90% power to detect a walk test difference of 240 ft and 83% power to detect MLHF score difference of 12.5 between groups, each of which is half the magnitude of difference observed in the pilot study. These differences represent clinically meaningful changes in functional capacity and quality of life.

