### Statistical Analysis and Power

Prior to analyzing the outcomes, we will compare the randomized groups with respect to baseline demographic, functional, and clinical variables as well as known prognostic factors (such as baseline NYHA class and baseline peak VO2) using chi-square and Fisher’s exact tests. Although we do not expect any differences with proper randomization, any significant imbalances (p<.05) will be adjusted for in the statistical analyses. All analyses will be performed on an intention-to-treat basis.

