## Procedures for obtaining Informed Consent

Written informed consent will be obtained by the research nurse coordinator, the research assistant, or study investigator prior to or during this initial visit. Patients will be asked to participate in a study comparing Tai Chi to a HF education intervention. Patients who are unable to complete a baseline bicycle stress test (e.g., have unexpected ischemic changes or life-threatening arrhythmias during testing) will be excluded, although this circumstance is expected to be rare. Randomization will therefore take place after baseline testing. Treatment assignments will be generated by a permuted blocks method with randomly varying block size and sealed in numbered, opaque envelopes. Randomization will be stratified based on NYHA heart failure class (class I/II versus class III). Once final eligibility is confirmed, the research nurse coordinator or unblinded research assistant will open the next envelope in sequence and the patient will be informed of assignment.

##

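### Randomisation is stratified by NYHA class but the primary test is not, so the test is conservative and forgoes power to the extent that NYHA class predicts 12-week change

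*Protocol*

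**What the plan says.** Under Procedures for obtaining Informed Consent: "Randomization will be stratified based on NYHA heart failure class (class I/II versus class III"). This is the only stratification factor named. The same section states: "Treatment assignments will be generated by a permuted blocks method with randomly varying block size".

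The Analysis Plan for Primary Specific Aims has two branches for the three primary endpoints. The default is "performing two-sample non-parametric Wilcoxon rank-sum tests to compare the distribution of change from baseline to 12 weeks between treatment and control groups". The other depends on a preliminary Kruskal-Wallis test: "In the event that we observe a site effect, we will proceed stratifying our analyses by site using van Elteren’s test". NYHA class is in neither branch.

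Statistical Analysis and Power counts NYHA class among the "known prognostic factors (such as baseline NYHA class and baseline peak VO2"), but the only route from there into the outcome analysis is that "any significant imbalances (p<.05) will be adjusted for in the statistical analyses". The Analysis Plan for Secondary Aims uses the same kind of Wilcoxon test for change in neurohormonal markers, other quality of life, mood and self-efficacy. It names NYHA class as a covariate only in the cost regressions.

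**The concern.** Blocking within NYHA strata removes most of the chance difference in NYHA mix between the arms. The null variance used by the unstratified rank-sum test assumes that this difference is still there. If NYHA class predicts the change score, the test statistic varies less than its reference distribution, so the test rejects too rarely under the null. A test that compares patients within strata would use the same data more efficiently.

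The plan is ready to stratify by site, which was not a randomisation factor and for which it expects no effect, but not by the factor on which it randomised. The imbalance rule does not help: the better the stratified randomisation works, the less likely an I/II-versus-III imbalance is to reach p<.05.

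**Working it through.** **Inputs from the protocol.** "We will enroll a total of 100 patients, with 50 patients in each group", with 20% dropout: 100 × 0.8 = 80 completers, 40 per arm. Peak VO2 effect 1.5 ml/kg/min, SD of change 2.1: standardised effect 1.5/2.1 = 0.714. Three endpoints and "we will apply a Bonferroni adjustment to preserve the 5% level of significance": 0.05/3 = 0.0167 per endpoint. Two-sided testing is assumed (z = 2.394), since sidedness is not stated.

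**Assumptions, because the protocol gives neither.** The share p of patients in class III, and the gap g between classes in mean 12-week change, in units of the total SD. For scale, g = 1.0 means that the classes differ in mean change by 2.1 ml/kg/min of peak VO2 or 317 ft of walk distance. Both exceed the treatment differences targeted (1.5 ml/kg/min and 240 ft).

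**The protocol's own figure.** It states no size or power for this mismatch. Its nearest figure is 80% power for peak VO2. With 50 × 0.8 × 0.9 = 36 effective patients per arm, Φ(0.714 × √(36/2) − 2.394) = Φ(0.64) ≈ 74%. That difference is a separate matter and plays no part here.

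**Size, by approximation.** With total SD fixed, the share of variance explained by the stratum is R² = p(1 − p)g². If blocking removes the between-stratum part, the true size of the unstratified test is about 2[1 − Φ(2.394/√(1 − R²))]. For p = 0.30:
- g = 0.25: R² = 0.3 × 0.7 × 0.0625 = 0.013; size about 1.6%
- g = 0.5: R² = 0.053; 2.394/0.973 = 2.46; size about 1.4%
- g = 1.0: R² = 0.21; 2.394/0.889 = 2.69; size about 0.7%

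Simulations at g = 1.0 give about 0.6 to 1.1%, in line with this.

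**Power, by simulation.** Normal outcomes, 80 completers (56 in class I/II, 24 in class III), permuted blocks within strata, total SD fixed, effect 0.714 SD. The 0.25 row is from a separate run of the same set-up.

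| Gap g | Unstratified Wilcoxon | van Elteren by NYHA | Difference |
|---|---|---|---|
| 0 | 73.5% | 73.3% | −0.2 |
| 0.25 | 74.0% | 73.7% | −0.3 |
| 0.5 | 74.9% | 76.4% | +1.5 |
| 1.0 | 75.6% | 83.7% | +8.1 |

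**Other class III shares**, unstratified then stratified:

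| Share | g = 0 | g = 0.5 | g = 1.0 | Unstratified size at g = 1.0 |
|---|---|---|---|---|
| 20% | 73.9%, 73.4% | 74.1%, 75.0% | 75.5%, 81.3% | 0.95% |
| 35% | 74.8%, 73.6% | 74.5%, 76.7% | 76.9%, 85.6% | 0.70% |
| 50% | 74.9%, 74.1% | 74.4%, 76.2% | 76.8%, 86.9% | 0.50% |

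In these three sets of runs the stratified test's size lies between 1.5% and 1.8%, which is nominal within simulation error. The simulations block the completers directly. Real dropout would loosen the balance a little and make the unstratified test somewhat less conservative.

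**The case against.** **The condition may not be met.** What matters is whether NYHA class predicts 12-week change. The protocol calls the class prognostic but does not say that it predicts change, and a change score removes much of the baseline difference between classes. This stands. At gaps up to 0.25 SD nothing is gained, and the 8-point figure needs a gap larger than the treatment effect sought.

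**Protection against chance imbalance is kept.** This also stands. That purpose of stratifying is served whatever the test, and only the efficiency part is at issue.

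**A statistical analysis plan might add the stratum.** It might, but the protocol does not leave the test open: it names the test and the one permitted stratification.

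**A larger loss is tempting to compute.** If the within-stratum SD is held at 2.1 and a 1.0 SD gap is added on top, unstratified power falls to about 65% against about 73% stratified. But this raises the total SD to 2.1 × √1.21 = 2.31. The stated 2.1 is the pilot SD of change, and Possible Risks says that the pilot used the same eligibility criteria. If the pilot enrolled both strata, 2.1 already contains the variation between classes. With total SD fixed, unstratified power stays at about 74 to 77% across all gaps. The difference between the tests is therefore an unclaimed gain, not a fall below what the plan would otherwise have.

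**Conclusion.** The mismatch between design and analysis is real and its direction is clear: the planned test is conservative if NYHA class predicts change. For 30% in class III, the power forgone at the peak VO2 effect is about nil up to a 0.25 SD gap, 1 to 2 points at 0.5 SD and about 8 points at 1.0 SD. The split, the gaps and normal outcomes are assumptions. If there is no gap, stratifying costs at most about 1 point.

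Three stronger readings are not supported. A reader might infer that the primary p-values are invalid, but the error is on the safe side. A reader might infer that confidence intervals are too wide, but the primary analysis specifies rank tests and plans no intervals. A reader might infer that this explains why the stated power is hard to reproduce, but the shortfall is there with no NYHA effect at all. This is a modest efficiency improvement at almost no cost.

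**What to change.** In the Analysis Plan for Primary Specific Aims, name van Elteren's test stratified by the randomisation stratum (NYHA I/II versus III) as the primary test for all three endpoints, fixed before unblinded data are seen and not conditional on any preliminary test. If the site branch is kept, say that site is crossed with the NYHA stratum and does not replace it. In the Analysis Plan for Secondary Aims, use the same NYHA-stratified test for the Wilcoxon comparisons of change.

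The cost is about one sentence in each section. The test is already named in the protocol and the stratum is recorded at randomisation, so no new data, software or patients are needed.

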### Analysis Plan for Secondary Aims

For neurohormonal markers: BNP, TNF-alpha, c-reactive protein, and norepinephrine, two-sample Wilcoxon rank-sum tests will also be used to compare distribution of change from baseline to 12 weeks between intervention and control groups.

Scores on other quality of life, mood, and exercise self-efficacy assessments will be analyzed using similar tests: Wilcoxon rank-sum, comparing the change from baseline to 12 weeks between treatment and control groups. In addition, we will use linear regression models using primary study outcomes (change in six-minute walk, peak VO2, and MLHF score) as dependent variables and scores on these psychosocial assessments as predictors to examine whether clinical outcome is associated with quality-of-life, mood, or self-efficacy. Separate models will be developed for each primary outcome. In the Tai Chi intervention group, we will also describe patient attendance at classes and compliance with home practice and determine whether compliance is associated with either baseline exercise self-efficacy or a positive change in exercise self-efficacy.

Medical utilization costs of the two groups will be compared using Wilcoxon rank-sum tests, examining cost components (outpatient visits, telephone contacts, hospitalizations, radiology and laboratory tests, procedures, and medications) separately and in total. We will also use linear regression models to adjust for baseline patient characteristics, such as sociodemographic variables (race) or clinical variables (co-morbidities and NYHA class).

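### Rank-sum tests on raw change have no prespecified adjustment for the outcome's own baseline or the NYHA stratum, and the p<.05 imbalance rule does not fill the gap

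*Protocol*

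**What the plan says.** The protocol's Analysis Plan for Primary Specific Aims covers six-minute walk, peak VO2 and MLHF score. If no site effect appears, the analysis is a Wilcoxon rank-sum test that will "compare the distribution of change from baseline to 12 weeks between treatment and control groups for each outcome measure". If one appears, "we will proceed stratifying our analyses by site using van Elteren’s test". The Analysis Plan for Secondary Aims repeats the approach. For BNP, TNF-alpha, C-reactive protein and norepinephrine it states that "two-sample Wilcoxon rank-sum tests will also be used to compare distribution of change from baseline to 12 weeks between intervention and control groups". For the other quality-of-life, mood and self-efficacy scores the test is "Wilcoxon rank-sum, comparing the change from baseline to 12 weeks between treatment and control groups".

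Baseline adjustment appears in Statistical Analysis and Power. The groups are to be compared on baseline variables, including "known prognostic factors (such as baseline NYHA class and baseline peak VO2", and "any significant imbalances (p<.05) will be adjusted for in the statistical analyses". That section does not say how the adjustment would be made.

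The data needed are available. Under Measurement Protocols, walk, questionnaires and blood tests are done at baseline, 6 and 12 weeks, and the bicycle test at baseline and 12 weeks. Under Procedures for obtaining Informed Consent, randomisation follows baseline testing and is stratified by NYHA class (I/II versus III).

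**The concern.** A change score fixes the coefficient of the baseline value at 1. When the correlation between baseline and 12 weeks is below 1, this has two costs. The comparison is noisier than one that estimates the coefficient. Part of any chance baseline difference between the arms also passes into the comparison through regression to the mean. The NYHA stratum, which the design treats as important enough to stratify on, is likewise left out of the tests.

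The conditional rule does not remedy this. It makes the form of the analysis depend on a significance test of baselines that randomisation already balances in expectation. It leaves imbalances short of the threshold untouched. When it is triggered it has no stated method to use, because neither the rank-sum test nor van Elteren's test takes a continuous covariate. The adjusted analysis would then have to be devised during the trial or after it. With 100 patients and alpha split over three endpoints, precision that costs no patients is worth having.

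**Working it through.** **Inputs from Sample Size Justification.** 50 per group; 20% dropout; 10% efficiency loss for rank tests; Bonferroni over three endpoints, so alpha = 0.05/3 = 0.0167 (two-sided assumed, as sidedness is not stated). SDs of change: 2.1 ml/kg/min, 317 ft, 17 points. Differences: 1.5 ml/kg/min, 240 ft, 12.5 points.

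**Assumed, not in the protocol.** Baseline to 12-week correlation r from 0.5 to 0.9, and equal variances at the two times.

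**1. The plan's own power.** Effective n per arm = 50 × 0.8 × 0.9 = 36. Power = Φ(δ / (σ√(2/36)) − 2.394). For peak VO2: 1.5 / (2.1 × 0.2357) = 3.030, and Φ(0.636) = 73.8%. The walk test gives 79.3% and MLHF 76.6%. The protocol states 80%, more than 90% and 83%, so its figures are not reproduced from its inputs (a noncentral t calculation gives 71.7, 77.4 and 74.6%). That is a separate matter; here 73.8 / 79.3 / 76.6% is only the reference.

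**2. Gain in precision.** With common variance s², Var(change) = 2(1−r)s² and the variance after adjustment for baseline is (1−r²)s². The ratio is (1−r²) / [2(1−r)] = (1+r)/2. Multiplying each SD of change by √((1+r)/2) in the formula of step 1 gives:

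| | Variance ratio | Peak VO2 | Walk | MLHF |
|---|---|---|---|---|
| Protocol states | – | 80% | >90% | 83% |
| Change score | 1.00 | 73.8% | 79.3% | 76.6% |
| r = 0.9 | 0.95 | 76.3% | 81.6% | 79.0% |
| r = 0.8 | 0.90 | 78.8% | 83.9% | 81.4% |
| r = 0.7 | 0.85 | 81.4% | 86.2% | 83.9% |
| r = 0.6 | 0.80 | 84.0% | 88.4% | 86.3% |
| r = 0.5 | 0.75 | 86.5% | 90.6% | 88.7% |

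The gain runs from 2.3 points (walk, r = 0.9: 81.6 − 79.3) to 12.7 points (VO2, r = 0.5: 86.5 − 73.8).

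**3. What the p<.05 rule misses.** With 50 per arm, a baseline difference just short of p<.05 is about 1.96 × √(2/50) = 0.39 baseline SD. The baseline SD implied by the SD of change is σ / √(2(1−r)). Given a baseline difference D, the difference in change shifts by (1−r)D in size. For peak VO2 at r = 0.5: baseline SD = 2.1, D = 0.392 × 2.1 = 0.82, shift = 0.5 × 0.82 = 0.41.

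| r | VO2 (ml/kg/min) | Walk (ft) | MLHF (points) | Share of design difference |
|---|---|---|---|---|
| 0.5 | 0.41 | 62 | 3.3 | 26–27% |
| 0.7 | 0.32 | 48 | 2.6 | 20–21% |
| 0.8 | 0.26 | 39 | 2.1 | 16–17% |
| 0.9 | 0.18 | 28 | 1.5 | 12% |

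These shifts are for an imbalance right at the threshold; smaller imbalances shift the result in proportion.

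**The case against.** The plan is coherent in its own terms. It defines the endpoints as change, bases power on SDs of change and budgets 10% for the rank test. Under randomisation the test is valid. All of this stands, and it makes the point one of efficiency and prespecification.

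The conditional rule is a real answer in part. A reader might infer that baseline is never adjusted for. The protocol does not support that: it promises adjustment for significant imbalances and names baseline peak VO2, itself the baseline of a primary endpoint. What remains is that the rule is triggered by a test, has no method, and misses imbalances below the threshold.

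A reader might also infer that every secondary comparison is affected. For costs the protocol says "Medical utilization costs of the two groups will be compared using Wilcoxon rank-sum tests", does not describe a change score, and adds regression on baseline patient characteristics. Costs are outside the point.

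The ratio (1+r)/2 compares two linear analyses, while the planned test is rank-based, and the calculation keeps the 10% rank allowance throughout. The powers are therefore approximate and match neither proposed analysis exactly. For the biomarkers, ranking already limits the influence of extreme changes, and no distributions are given, so no claim is made that high baselines dominate those tests. Nor is the lack of a stated effect estimate or interval part of the point, since that may sit in a statistical analysis plan that was not available.

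**Conclusion.** The point holds as an avoidable loss of precision and an incompletely specified adjustment. It should be changed, but it does not make the trial invalid. For r of 0.5 to 0.9, adjustment lowers variance by 5 to 25% and adds roughly 2 to 13 points of power. A threshold-level imbalance left unadjusted would shift the comparison by about 12 to 27% of the design difference.

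Two stronger readings are not supported. One is that the change-score comparison is biased: it is unbiased over randomisations, and only (1−r) of a baseline difference that has actually occurred enters the result. The other is that adjustment would restore the stated powers. Peak VO2 and MLHF reach theirs at r of 0.7 or below but not at 0.8, and the walk test stays under 90% for r of 0.6 or above.

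The sizes rest on an assumed r, equal variances, a two-sided alpha of 0.0167 and a linear-model approximation. The direction does not depend on the value of r: under equal variances (1+r)/2 is below 1 for any r below 1, apart from a negligible cost in degrees of freedom.

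**What to change.** Prespecify the following, whatever any baseline comparison shows:

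- **Primary endpoints.** For each, regress the 12-week value on arm, the baseline value of that endpoint and the NYHA stratum. To keep the non-parametric intent, use rank analysis of covariance with the same covariates.
- **Secondary outcomes now tested as change.** Use the same form, with biomarkers on the log scale adjusted for log baseline, or by rank analysis of covariance.
- **Wilcoxon test on change.** Keep it as a supportive analysis.
- **Statistical Analysis and Power.** Remove the p<.05 trigger; baseline comparisons can remain as description. Reword the site-effect fallback to fit the new primary analysis.

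The cost is a small change of analysis wording and an update of Sample Size Justification, whose SDs of change and 10% rank allowance belong to the present test. No extra measurements or patients are needed. The update should state the assumed baseline to 12-week correlation, from the pilot data if they provide it.
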